## Abstract

Background

Caregivers of children with congenital heart disease (CHD) often experience stress, uncertainty, and challenges in managing their child’s care after hospital discharge. A structured transition care approach can help ease this process by improving caregivers' preparedness, awareness, and satisfaction with post-discharge care.

Objective

This study aims to develop and evaluate a nurse-led transition care guidance (TCG) program to enhance caregivers' readiness, awareness, and satisfaction during the transition from hospital to home care for children with CHD.

Method

A mixed-methods approach was used, consisting of a quasi-experimental quantitative phase to assess the effectiveness of the TCG intervention by comparing caregivers' readiness and satisfaction scores before and after implementation and qualitative focus group discussions (FGDs) to explore caregivers' unmet needs and challenges during the transition process.

Data sources include caregiver surveys, post-discharge follow-up interviews, and hospital records. Thematic analysis will be conducted on FGDs to identify key issues affecting caregivers.

Results

The intervention is expected to improve caregivers' ability to provide care, increase their understanding of medical needs, and enhance their overall satisfaction with the transition process. Qualitative findings will highlight common challenges and gaps in post-discharge support.

Conclusion

This study will contribute to the development of evidence-based transition care plans that optimize the hospital-to-home transition for children with CHD. It highlights the importance of structured, nurse-led interventions to improve post-discharge outcomes for both caregivers and patients.

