## Materials and methods

This study will have a mixed-methods design, incorporating both qualitative and quantitative approaches to address the research questions. The qualitative phase will involve focus group discussions (FGDs) with caregivers, nurses, and physicians to understand the challenges and unmet needs faced by caregivers during the transition of children with CHD from hospital to home. Multi-stakeholder opinion on transition care will help identify the gaps in caregiver preparedness and inform the development of the nurse-led TCG program. The qualitative data will be analyzed using thematic analysis, which will allow the identification of common themes and patterns in the experiences and challenges reported by the participants.

In the quantitative phase, a quasi-experimental design with a pre-test and post-test control group will be used to evaluate the effectiveness of the nurse-led TCG program. The intervention group will receive the TCG program, which will include pre-discharge education sessions, personalized discharge care guides, and telephonic follow-up support at specified intervals post-discharge. The control group will receive standard discharge instructions without the additional components of the TCG program.

The study will take place in the pediatric care units of a tertiary care hospital. The participants will include caregivers of children diagnosed with congenital heart disease who are preparing for discharge. Inclusion criteria will include caregivers who are the primary decision-makers and care providers for the child and caregivers of children with congenital heart disease who are scheduled for discharge from the pediatric care unit. Exclusion criteria will include caregivers who have limited language proficiency, caregivers who are unable to attend the intervention sessions, and caregivers who are unable to commit to the follow-up process due to logistical or other reasons.

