The control group will receive the standard discharge care provided by the hospital, which includes routine discharge instructions given by healthcare providers before the child is discharged. This typically consists of verbal guidance on medication administration, follow-up appointments, basic home-care instructions, and emergency signs to watch for. However, caregivers in the control group will not receive the additional structured components of the nurse-led TCG program. Specifically, they will not have access to personalized discharge care guides, structured pre-discharge education sessions, or scheduled telephonic follow-up support.

The control group caregivers will still undergo a pre-discharge assessment to evaluate their initial knowledge and readiness for discharge. During the follow-up period, their experiences and post-discharge outcomes will be assessed at 7, 15, 30, and 45 days after discharge through surveys and telephone interviews. Data from the control group will serve as a baseline for comparison with the intervention group to determine the effectiveness of the TCG program in improving caregiver preparedness, confidence, and child health outcomes.

The nurse-led TCG program will be developed based on the findings from the qualitative phase and will focus on key areas, such as medication administration, signs of deterioration, feeding techniques, emergency management, and other essential aspects of post-discharge care. The program will also include the provision of a personalized discharge care guide, which will contain instructions on daily care, emergency contact numbers, follow-up schedules, and signs to watch for in the child’s health. Additionally, caregivers in the intervention group will receive telephonic follow-up at 7, 15, 30, and 45 days post-discharge to ensure they have the opportunity to ask questions, reinforce learning, and receive additional support as needed.

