The primary outcome measures for this study will include caregiver knowledge of CHD and its management, caregiver readiness for discharge, and caregiver satisfaction with the transition process. Caregiver knowledge will be assessed using a congenital heart disease knowledge scale (CHDKS), which will be developed specifically for this study and validated for reliability and accuracy before data collection. Similarly, caregiver readiness for discharge will be evaluated using a readiness for discharge scale, which will be developed and subjected to rigorous validity and reliability testing. Caregiver satisfaction will be measured through a satisfaction survey assessing their experience with the discharge process, the information provided, and the support received; this tool will also undergo validity and reliability testing before implementation. All research instruments will be carefully developed and tested for content validity, construct validity, and reliability to ensure accurate and meaningful measurement of study outcomes.

Secondary outcomes will include caregiver confidence in managing care tasks, including medication administration and recognizing emergency signs in the child, as well as hospital readmission rates and post-discharge complications within 30 days of discharge. A caregiver confidence assessment tool will be developed specifically for this study and validated for reliability and accuracy before data collection. Hospital readmission rates and post-discharge complications will be tracked using hospital records and follow-up interviews. These outcomes will help assess the broader impact of the nurse-led TCG program on both caregiver preparedness and child health outcomes.

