Data collection will be conducted at three time points: baseline (at the time of admission), during discharge, and post-discharge follow-up (starting from seven days after discharge). At baseline (admission), caregiver surveys will be conducted to assess their initial knowledge, readiness, and confidence in managing care. During discharge, post-assessment will be carried out to evaluate changes in caregiver preparedness and understanding after receiving the nurse-led TCG. Post-discharge follow-up, starting from seven days after discharge, will involve caregiver surveys, telephone interviews, and a review of medical records to track hospital readmission rates and post-discharge complications up to 45 days after discharge. The qualitative data will be collected through FGDs, which will be audio-recorded, transcribed, and analyzed using thematic analysis. Quantitative data will be analyzed using statistical methods such as paired t-tests for comparing pre- and post-intervention measures, independent t-tests to compare the intervention and control groups, and multiple regression analysis to identify predictors of caregiver satisfaction and readiness for discharge.

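### The article gives conflicting accounts of how effectiveness is judged: the abstract uses before-after scores, including a satisfaction pre-score that is not collected, while the methods rest on TCG versus control

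*Protocol article*

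**What the plan says.** The protocol article describes the assessment of effectiveness in several places, and they do not agree.

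- **Abstract, Method.** Effectiveness is assessed by comparing "readiness and satisfaction scores before and after implementation". No control group is mentioned.
- **Materials and methods, design.** "a quasi-experimental design with a pre-test and post-test control group will be used to evaluate the effectiveness" of the programme. The section later adds: "Data from the control group will serve as a baseline for comparison with the intervention group to determine the effectiveness of the TCG program".
- **Materials and methods, analysis.** One sentence lists "paired t-tests for comparing pre- and post-intervention measures", then "independent t-tests to compare the intervention and control groups", then multiple regression for predictors of satisfaction and readiness. It does not assign the t-tests to outcomes or say which one decides.
- **Materials and methods, data collection.** At admission, "caregiver surveys will be conducted to assess their initial knowledge, readiness, and confidence in managing care". Satisfaction is not on that list.
- **Materials and methods, outcomes.** The satisfaction survey asks about "experience with the discharge process, the information provided, and the support received".
- **Results (expected).** Knowledge and satisfaction are hypothesised to be higher than in controls. The readiness hypothesis opens as an improvement within the intervention group, and its follow-up sentence names no comparator.

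**The concern.** Two definitions of effectiveness are in play, and they answer different questions. A before-after change in the TCG group mixes the programme's effect with everything else that happens between admission and discharge. Materials and methods says controls receive routine verbal instruction on medication, appointments, home care and warning signs. That overlaps with the programme's content, so knowledge and readiness can be expected to rise without the programme. A paired test in the TCG group makes no use of the controls and cannot separate the two sources.

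If the abstract's definition were followed, a significant rise could be reported as effectiveness although controls had risen by as much. For satisfaction the abstract's comparison also lacks its first measurement.

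**Working it through.** **Which comparison decides?** The abstract says before versus after. The design and control-group paragraphs say TCG versus control. The analysis sentence permits both without ranking them. The expected Results follow the controls for knowledge and satisfaction, and begin within-group for readiness. The contradiction concerns the primary aim.

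**Is there a satisfaction pre-score?** The admission survey lists knowledge, readiness and confidence only. The satisfaction survey asks about a discharge process that has not happened at admission. So no before value exists for the same caregiver. If the abstract meant separate cohorts before and after roll-out, a paired test would not apply either, and that reading would conflict with the control-group design.

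**How often is the paired test significant with no programme effect?** The article gives no sample size, SD, expected gain or correlation, so there is no stated figure to reproduce and all inputs here are assumptions: ordinary gain *g* of 0.2 to 0.8 SD, pre-post correlation *ρ* of 0.3 to 0.7, *n* of 20 to 100 per group, two-sided 5% level.

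- Standardised mean change: d_z = g / √(2(1 − ρ)). At ρ = 0.5 the denominator is 1, so d_z = g.
- Noncentrality: d_z√n, with n − 1 degrees of freedom. At n = 50 (√50 = 7.071) this is 1.41, 2.12 and 3.54 for g = 0.2, 0.3 and 0.5.
- Rejection probability is taken from the noncentral t distribution.

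Results at ρ = 0.5, true programme effect zero:

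| Ordinary gain | n = 20 | n = 30 | n = 50 | n = 100 |
|---|---|---|---|---|
| 0.2 SD | 13.6% | 18.5% | 28.4% | 50.8% |
| 0.3 SD | 24.7% | 35.5% | 54.8% | 84.4% |
| 0.5 SD | 56.5% | 75.4% | 93.4% | 99.9% |
| 0.8 SD | 92.4% | 98.8% | 100.0% | 100.0% |

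At n = 50, the values for gains of 0.2, 0.3 and 0.5 SD are 21.6%, 42.0% and 83.4% with ρ = 0.3, and 43.3%, 76.6% and 99.4% with ρ = 0.7.

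**What does the between-group test do in the same situation?** In 20,000 simulated studies with g = 0.5, ρ = 0.5 and no programme effect, the control group's paired test was significant as often as the TCG group's (about 75%, 93% and 99.9% at n = 30, 50 and 100). The independent t-test rejected in about 5%, on post scores or on change.

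**Why adjust for baseline?** That 5% presumes comparable groups, and allocation is not randomised. With an assumed baseline imbalance of 0.3 SD, the expected post-score difference is 0.5 × 0.3 = 0.15 SD with no programme effect. The unadjusted post-score t-test then rejected in 8%, 11% and 19% at n = 30, 50 and 100. In this set-up the whole difference passes through the measured baseline, so ANCOVA on that score removes it.

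**The case against.** The strongest reply is that the plan already contains the right comparison. The sentence that lists paired t-tests goes on to independent t-tests between groups, the control data are expressly meant to determine effectiveness, and two of the three primary hypotheses are stated against control. The list of tests is illustrative, in a condensed article whose analysis plan is not shown. Which test is confirmatory is often left to that plan. All of this stands, and it limits the point.

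A reader might infer four stronger things that the article does not support:

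- **That effectiveness will be judged by paired t-tests.** The methods point the other way. What is true is that the deciding test is not fixed and the abstract names the wrong comparison.
- **That the paired test is bound to be significant.** This depends on the sample size, gain and correlation, none of which is given.
- **That significance will be compared across groups**, with a significant TCG group and a non-significant control group read as proof. The article nowhere proposes this.
- **That the methods apply paired tests to satisfaction.** The analysis sentence names no outcome and can be carried out for knowledge, readiness and confidence. The satisfaction problem comes from the abstract.

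What the reply does not answer is the contradiction itself. An unseen analysis plan can add detail, but the published abstract would still define effectiveness as a before-after change and refer to a score that is not collected.

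**Conclusion.** The point holds as an inconsistency in the definition of effectiveness, together with a satisfaction comparison that cannot be made on the same caregivers. It is not a fault in the design, which has a control group and a between-group test.

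If the before-after definition were used, the chance of a significant result with no programme effect would be about 28% to 93% at n = 50 and correlation 0.5, for ordinary gains of 0.2 to 0.5 SD. Over the whole assumed grid it runs from about 11% (0.2 SD, correlation 0.3, n = 20) to practically 100%. The exact size is therefore uncertain. That a paired test in one group cannot isolate the programme does not depend on those assumptions. The point should be corrected, but as clarification, not as a defect that undermines the study.

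**What to change.** 1. State in Materials and methods that effectiveness is concluded only from the TCG-versus-control contrast.
2. For knowledge, readiness and confidence, replace the unadjusted independent t-tests with ANCOVA of the post score on group and admission score. This requires the admission survey in both groups; the data-collection paragraph does not restrict it to one.
3. For satisfaction, compare post scores between groups, adjusted for caregiver and child characteristics, because there is no baseline and the groups are not randomised.
4. Label paired t-tests as descriptions of within-group change that carry no effectiveness claim.
5. Reword the abstract to the between-group comparison and remove satisfaction from any before-after statement. Word the readiness hypothesis in Results against control.

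The cost is wording. No visit or instrument is added. The planned regression for satisfaction and readiness already implies that some caregiver or child characteristics will be recorded. Adjustment removes only the imbalance that the recorded variables capture, and the report should say so.

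### The group comparison in a non-randomised study is assigned to unadjusted t-tests, so any baseline or case-mix difference would bias the estimated programme effect in either direction

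*Protocol article*

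**What the plan says.** All the relevant text is in the Materials and methods section of the protocol article.

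- **Design:** "a quasi-experimental design with a pre-test and post-test control group will be used to evaluate the effectiveness of the nurse-led TCG program". No randomisation, matching or other means of making the groups comparable is described. Eligibility is not restricted by severity of disease or by surgery.
- **Baseline data:** "At baseline (admission), caregiver surveys will be conducted to assess their initial knowledge, readiness, and confidence in managing care". Satisfaction is not in this list.
- **Methods:** the sentence opens "Quantitative data will be analyzed using statistical methods such as paired t-tests", so the list is illustrative, and it gives each method a purpose. Paired t-tests are for change within a group. The group comparison and the regression are described as "independent t-tests to compare the intervention and control groups, and multiple regression analysis to identify predictors of caregiver satisfaction and readiness for discharge".
- **Use of the control group:** it is the comparator by which effectiveness is to be determined. The three primary outcomes are knowledge, readiness and satisfaction.

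**The concern.** An independent t-test estimates the programme effect only if the two groups would have had the same mean outcome without the programme. Randomisation would justify that, but this design does not provide it. The groups may differ in what caregivers already knew, in their education, or in how complex the child's heart disease is. Any such difference that is related to the outcome passes into the estimate.

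The one named method that could adjust for this, multiple regression, is assigned to finding predictors of two outcomes. It is not named as the estimate of the programme effect, and it does not mention knowledge. The paired t-tests do not help, because they describe change within a group and do not estimate the difference between groups.

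At stake is the main conclusion of the quantitative phase. A group difference in scores, or its absence, could not be separated from differences that existed before the programme began.

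**Working it through.** **What the article supplies.** It gives the design, the methods and the list of admission measures. It states no sample size, significance level, standard deviation, expected effect or correlation, so there is no figure of the plan's own to reproduce. The numbers below are illustrations on assumed inputs.

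**Assumptions.** Scores are in SD units with equal variance. The groups differ by d at admission, the pre-post correlation is r, and the programme has no effect. The post score depends on group only through the admission score, so the expected post score is r × the admission score. Tests are two-sided at 5%, with n caregivers per group.

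**Bias**

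- t-test on post scores: r × d.
- t-test on change scores: r × d − d = (r − 1) × d.

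For 0 < r < 1 and d not zero, neither is zero, and the two have opposite signs. If the intervention group starts higher, the post-score test overstates the effect and the change-score test understates it. If it starts lower, both reverse.

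**Rejection rate, post scores.** The noncentrality parameter is bias × √(n/2), with 2n − 2 degrees of freedom.

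| n per group | d | r | Bias (SD) | Noncentrality | Rejection rate |
|---|---|---|---|---|---|
| 50 | 0.3 | 0.5 | 0.15 | 0.15 × 5 = 0.75 | 11.5% |
| 50 | 0.5 | 0.5 | 0.25 | 0.25 × 5 = 1.25 | 23.6% |
| 50 | 0.5 | 0.7 | 0.35 | 0.35 × 5 = 1.75 | 41.0% |
| 100 | 0.3 | 0.5 | 0.15 | 0.15 × 7.07 = 1.06 | 18.4% |
| 100 | 0.5 | 0.7 | 0.35 | 0.35 × 7.07 = 2.47 | 69.2% |
| 30 | 0.2 | 0.3 | 0.06 | 0.06 × 3.87 = 0.23 | 5.6% |

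The last row matters as much as the others: with a small imbalance and a weak correlation the rate is almost nominal. For a given bias, a larger sample raises the rate.

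**Rejection rate, change scores.** The SD of a change score is √(2(1 − r)), so the noncentrality parameter is (r − 1) × d × √(n/2) / √(2(1 − r)). With n = 50, d = 0.5 and r = 0.5, the bias is −0.25 SD and the rate is again 23.6%. With n = 50, d = 0.3 and r = 0.7, the bias is −0.09 SD and the rate is 8.9%.

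**Adjusting for the admission score.** In simulations of 4,000 runs per setting with n = 50 and r = 0.5:

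| d | t-test on post scores | ANCOVA (post score on group and admission score) |
|---|---|---|
| 0.3 | 11.1% | 4.9% |
| 0.5 | 22.5% | 4.6% |

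The mean ANCOVA estimate was about 0 in both settings. This holds because the admission score is the only confounder in the simulation. If instead the whole difference d persisted to the post score for other reasons, ANCOVA on the admission score alone would leave d − r × d = (1 − r) × d. That is why other characteristics belong in the model, and why adjustment is not a complete cure.

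**The case against.** Five points can be made for the plan.

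1. **The list of methods is open, and a condensed article may leave the adjusted model to a fuller document.** This is right as far as it goes: adjustment is not excluded, and silence about covariates would be no finding. The point rests on what the article does state, which is a between-group method that does not suit the stated design, with regression given another purpose.

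2. **A reader might infer that the t-test ignores the admission scores.** The article does not support that. It does not say whether post scores or change scores are compared, and change scores would use the pre-test. This alters the size and sign of the bias but does not remove it. For satisfaction, with no listed pre-test, no change score could be formed.

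3. **Study group could be entered as a predictor, which would give an adjusted coefficient for satisfaction and readiness.** The text permits this but does not say it, and knowledge would still not be covered.

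4. **A reader might infer that existing differences will be counted as benefit, or that effectiveness cannot be supported at all.** Neither follows. No imbalance has been shown, and one could as easily hide an effect as create one.

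5. **The illustrative rates are wholly assumed.** That is so. They show how the method behaves and are not evidence about this study.

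It could also be said that an unadjusted test is less precise than it need be. That is a matter of efficiency and is not relied on here.

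**Conclusion.** The concern holds in a limited form. The article fixes a non-randomised design with no stated balancing, and the only method it names for the effectiveness comparison has no adjustment. Any baseline or case-mix difference would bias the result by r × d for post scores or (r − 1) × d for change scores, so the direction is unknown. With post scores, no true effect, d of 0.3 to 0.5 and r of 0.5 to 0.7, a 5% test rejects about 12% to 41% of the time at 50 per group. Every one of those inputs is an assumption, and small imbalances take the rate back towards 5%. The weakness affects the named group comparison of all three primary outcomes. It can be largely repaired with admission scores that the study already plans to collect.

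**What to change.** In the analysis text of Materials and methods, name the effectiveness analysis of each primary outcome as a regression (ANCOVA) of the post score, with group as the effect of interest, adjusted for:

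- the admission score on the same scale for knowledge and readiness;
- the admission knowledge, readiness and confidence scores for satisfaction, which has no listed pre-test;
- a short list of characteristics settled at or before admission and fixed before data are seen, for example caregiver education, child age and complexity of the heart disease.

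Do not adjust for length of stay or other items settled after the admission baseline, because the programme could affect them. Surgery in the same admission belongs in the model only if it precedes the baseline assessment.

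Report the adjusted mean difference with a 95% CI, keep the unadjusted t-test as descriptive, and state that unmeasured confounding remains.

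The cost is a change of wording, a little more analysis and a few routine items from hospital records. No extra participants are needed.
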